### Sampling and recruitment

A multistage simple random sampling technique will be used to select 170 eligible women with disabilities from each of the study districts. This will involve several steps as described below.

#### Identification and enumeration

To ensure that women with disabilities from different backgrounds (e.g. rural vs. urban, and literate vs. non-literate) are represented in our study, we will conduct a comprehensive community level identification and enumeration of all sexually active reproductive aged women who identify themselves or are identified by family members as having some disability. This community level enumeration is important because although the Ghana Federation of Disability Organisations, local district assemblies, and other disability groups often have some database of registered members, our engagement with leaders of various disability groups in the study districts showed that this data is not sufficient as many persons with disabilities are often not registered with either the district assembly or the Ghana Federation of Disability Organisations. Therefore, a community level enumeration allows for identification of all potentially eligible participants.

To effectively undertake the community level enumeration, community health volunteers will be engaged in each of the study districts to do a house-to-house listing of all women with disabilities aged 15–49 years who have physical or visual disabilities. We propose to use community health volunteers because disability in Ghana still carries considerable stigma such that using a ‘stranger’ to do this household enumeration may be less successful [22, 24]. However, as community health volunteers are community members who may be well known and trusted because of the roles they already play in serving as a link between the formal healthcare system and local communities, women with disabilities and their families are likely to better cooperate.

We will design a simple *Enumeration Form* and train community health volunteers to use the form to enlist all women with physical and visual disability in their respective communities. The form will ask for basic information such as name, community, age, contact number, house number/name, disability type, and whether the disabled woman/girl is sexually active (i.e. have had penetrative sex before). Each of the women with disabilities would also be asked if she would be interested in taking part in the larger study, which will last for a period of 12 months.

In addition to using the enumeration form, we will also train the community health volunteers to administer an adapted screening tool from the Washington Group on Disability Statistics [6]. This screening tool has been successfully used in other low-income contexts to screen and identify women with disabilities [6]. The tool has 35 questions to detect disability type and social function and communication disabilities based on the International Classification of Functioning, Disability and Health [6]. The screening tool captures severity of disability by asking respondents to rank their status on a four-point Likert scale [6]. This tool will allow us to not only identify women/girls with disability but to determine the severity of their disability.

#### Screening

Following the identification and enumeration of all women with physical and visual disabilities in the study districts, we will screen to identify potentially eligible participants. The key considerations will be age (i.e. 15–49 years), disability type (i.e. physical, including albinism and leprosy, and visual disability), and whether the disabled woman/girl has had penetrative sex before.

#### Sampling

Following from the screening, we will create a register of all eligible participants in each district, subdivided along the lines of the two main forms of disabilities described earlier. Depending on the number of eligible participants in each category of disabilities, the total sample size of 170 per district will be proportionately divided among the different categories of disabilities. This means that sampling will be done proportionate to size, so that categories of disabilities with higher numbers of eligible participants are sampled more into the survey. Following from this, each of the eligible participant in each district and disability type will be given a unique number identifier (e.g. 001…00n). The numbered lists will then be imported, one list after the other, into a R statistical software, where the required number of respondents from each district (i.e. 170) and category of disability will be randomly selected.

#### Recruitment

In terms of the procedure for contacting and recruiting eligible women with disabilities into the survey, we will use the contact details collected during the enumeration phase alongside help from community health volunteers to contact all selected women with disabilities in their communities to further discuss the purpose of study and invite them to participate. Following this initial contact, each participant will be given 1 week to make a final decision on whether to participate in the study. They will each be re-contacted via telephone or other appropriate means after the 1-week period. All participants who will decline participation will be dropped and the sampling procedure repeated to get replacement from any remaining eligible potential participants. Where the list of eligible participants for any of the study districts is fully exhausted, there shall be no replacement.

### Data collection

A face-to-face interview method will be used to collect data from individual participants. A total of eight graduate research assistants will be recruited and trained to collect the data. Where feasible, all the research assistants will be persons with disabilities, and will be speakers of at least one of the local languages (i.e. *Dagbaani, Gonja* or *Moar*) in addition to English. They will also have previous experience of collecting survey data.

A structured questionnaire will be developed, pre-tested and used for data collection. The questionnaire will be developed in English, but the questions may be translated and asked in one of three local languages (i.e. *Dagbaani, Gonja* or *Moar*). The questionnaire will collect information to address the research objectives related to assessment of knowledge about modern family planning/contraceptives, and family planning/contraceptive use. Also, sociodemographic information of each respondent will be collected.

Several validated questions from the Ghana Demographic and Health Survey questionnaire [26] and the Ghana Maternal Health Survey questionnaire [31] will be used. These questions are related to the key outcome variable for the proposed study which is contraceptive use/uptake. Further, the questions will also assess awareness and knowledge of contraceptive use, contraceptive use negotiation, safe sex negotiation, use of multiple methods, use of antenatal care, and skilled delivery care services for respondents who have been pregnant or are currently pregnant as well as those who have given birth before. With regard to the primary outcome variable, contraceptive use/uptake, participants will be asked about their knowledge of family planning methods, and those who have ever heard about family planning will be asked about their use of family planning methods. Information on sexual and reproductive health information and education will also be collected. Most questions will be close-ended.

The questionnaire will be imported into the REDCap (Research Electronic Data Capture) platform (see https://projectredcap.org/software/)—a software used to design and collect electronic data using electronic gadgets such as mobile phones or tablet computers. This software allows the data to be collected and saved automatically on the device and uploaded unto an online server using internet while on the field. This technology will help minimise the potential for data loss which is common in the context of paper-based questionnaire, which could easily be destroyed by natural events such as rain or fire. Similarly, the automatic saving of the data makes it needless for a separate data entry phase common when paper-based questionnaires are used. However, poor internet access could affect the use of this technology. Therefore, we will procure high speed internet data to support this electronic data collection.

### Quality control measures

In order to ensure data quality, a number of measures will be implemented. All research assistants will be trained by the research team prior to data collection. During the training session, the research assistants will be taken through several aspects of the research and data collection tool, including explaining the main objectives of the study and the data collection techniques. During the training, the research assistants will be made to translate the questions into the relevant local interview language (i.e. *Dagbaani, Gonja and Moar*) to facilitate better understanding of the questions. Furthermore, the research assistants will undertake role-play exercises to help them have a better understanding of the questionnaires, and how to ask the questions appropriately during the actual data collection.

Following the training, the questionnaire will be pre-tested by the research assistants. The pre-test will help reveal likely problems that could arise during the actual data collection. It will also enable the research team to reframe unclear questions and to finalize the questionnaire before the start of actual data collection. In total, the questionnaire will be administered to 20 respondents (5 each in study district) in the pretest.

In addition, the research team will be actively involved in supervising the research assistants at each stage of the data collection to ensure that the data collection is properly done. Furthermore, the REDCap software that will be used for the data collection has inbuilt checks and branching logics that help to reduce data collection, entry and transmission errors.

### Data processing and analysis

Data from the online REDCap platform will be downloaded and exported as excel files. All data files will then be exported into STATA version 15 for cleaning, coding and possible recoding and analysis. Data cleaning will be done by identifying outliers/anomalies and checking for consistency among and across variables. Frequency distributions and cross tabulations will specifically be run to aid the data cleaning process. Basic descriptive statistical analyses will be performed to describe socio-demographic characteristics of respondents, as well as awareness about, and use of modern family planning/contraceptive methods.

In addition to using descriptive statistics to describe important characteristics and changes in SRH outcomes in each experimental arm, the main statistical analytical method will be Difference-in-Difference Analysis. This analytical technique will allow us to detect the true effect of each intervention in comparison to the control group, while controlling for confounders. The statistical analysis will particularly involve comparison of changes in key outcome variables across all arms of the experiment. In addition, Chi-square tests of association will be performed to understand factors associated with sexual and reproductive health services utilization, including examining association between a number of independent variables (e.g. age, sex, education, and disability type) and dependent variables (e.g. awareness about modern family planning/contraceptives, and use of modern contraceptives). Multiple logistic regression models will then be fitted to examine the relationship between dependent variables (e.g. modern contraceptive use) and independent variables. Furthermore, for continuous variables such as number of antenatal visits, multiple linear regression models will be fitted. Finally, cost-effectiveness analyses will be done on the three-intervention arms vis a vis changes in key outcome measures to identify which of the three interventions is likely to yield greater impact with lower costs. For all the inferential quantitative analysis, confidence level will be set at 95% and p-value of less than 0.05 will be taken as demonstrating statistical significance.

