## Methods

### Context

This research will be implemented in the Northern region of Ghana. As indicated earlier, the region has one of the highest unmet need for sexual and reproductive health services and the lowest supervised delivery rates in the country. For instance, while 25% of married women aged 15–49 years in Ghana used modern contraceptives in 2017, only 16.8% did so in the region [31]. The project would be implemented in four districts with the highest disability rates in the region: Central Gonja (3.6%), West Gonja (3.8%), Savlugu (4.6%), and Bunkprugu-Nankpanduri (5.4%) districts [32]. While the four districts chosen for the experiment are geographically distant enough to limit cross-contamination of participants, the districts are nevertheless socially, culturally and economically similar. This similarity will ensure comparability of results.

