### Design

A quasi-experimental quantitative study design, involving pre- and post-intervention surveys, will be used to test the effect of three inter-related interventions. Although evidence from designs such as cluster randomized clinical trial is typically at a much higher level than a quasi-experimental study, we chose a quasi-experimental design because the four study districts were purposively selected. Therefore, it was not possible to randomize the districts as clusters.

The inventions are *(1) capacity building in disability-centred sexual and reproductive health and rights information and services delivery for healthcare providers; (2) support for women with disabilities to access disability-unfriendly healthcare infrastructure and (3) one-on-one regular sexual and reproductive health and rights education, information provision, and referral*. While detailed description of each intervention is provided later, it is important to specify that the first two interventions are at the health-facility level while the third one is at the individual/family level.

In this quasi-experimental design, there are four arms; each to be based in one district determined using a simple random sampling procedure. In the first arm, eligible women with disabilities in the Savelugu Municipality will be exposed to all the three interventions. In the second arm, eligible women with disabilities in Bunkprugu-Nankpanduri district will be exposed to only the two-health facility-level interventions. The third arm (in Central Gonja District) will be exposed to only the individual level intervention. The forth arm (based in West Gonja district) will constitute the control group (i.e. women with disabilities will not be exposed to any intervention). To assess the effect of each of the three arms of interventions, we will first conduct a cross-sectional pre-intervention survey among all women with disabilities in each intervention arm. This survey will aim to collect baseline data on several outcomes including awareness about modern contraceptives, use of modern contraceptives, including antenatal care attendance and skilled delivery among those who have given birth before. The same survey will be repeated at the end of the intervention (i.e. 12 months) on the same women in all arms of the experiment.

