### Sample size estimation

To estimate a minimum sample size that will allow for small effect sizes to be detected, we used the sample size estimation formula below:$$n=Deff\times \frac{{\left\{Z_{1-\beta }\sqrt{ [p_{1}(1-p_{1} )+p_{2}(1-p_{2}) ]}+{Z}_{1-\alpha/2}\sqrt{\left[2\overline{p }(1-\overline{p })\right]}\right\}}^{2}}{(1-NR)\times {(p_{1}-p_{2})}^{2}} {Z}_{1-\alpha / 2}$$
where $${\overline{p}}={\frac{{p_1}+{p_2}}{2}}$$; $${p}_{1}=13.1\%,$$ which is the anticipated population proportion of modern contraceptive use at baseline based on a recent community-based cross-sectional study among women with disability in Ethiopia that estimated modern contraceptive use prevalence (a key outcome in the current study) [37]; $${p}_{2}=25.1\mathrm{\%},$$ which is the expected prevalence of modern contraceptive use after the implementation of the intervention; $${Z}_{1-\alpha/2}$$ in the formula is the standard normal variate at 5% level of significance; $$NR=10\%$$ is the anticipated non-response/loss to follow-up rate; Deff = 1.1 to adjust for design effect.

Based on these assumptions, the estimated sample size for each arm is 170. As the design contains four arms, the sample ratio is 1:1:1:1. This means that 170 women with disabilities will be recruited into each arm of the study, totalling 680.

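### Each arm is one district, so difference-in-difference cannot separate the intervention from district-specific change, and the claim to a true effect is wrong as written

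*Protocol article*

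**What the plan says.** **Structure.** The Design section states that "there are four arms; each to be based in one district determined using a simple random sampling procedure". Savelugu receives all three interventions, Bunkprugu-Nankpanduri the two facility-level ones, and Central Gonja the individual-level one. For the control: "The forth arm (based in West Gonja district) will constitute the control group". There are two time points: "The same survey will be repeated at the end of the intervention (i.e. 12 months) on the same women in all arms of the experiment".

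**Inference.** Data processing and analysis makes difference-in-difference the main method and says: "This analytical technique will allow us to detect the true effect of each intervention in comparison to the control group, while controlling for confounders". It applies a 5% significance threshold and 95% confidence to all inferential analyses. It names neither the unit of inference nor a standard-error method.

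**Comparability.** The Context section says "the districts are nevertheless socially, culturally and economically similar. This similarity will ensure comparability of results". The limitations paragraph of the Discussion repeats this.

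**Clustering.** Sample size estimation has "Deff = 1.1 to adjust for design effect", with no cluster level and no intraclass correlation (ICC).

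**Allocation.** Before the statement on simple random sampling, the Design section explains that the districts were purposively selected and concludes: "Therefore, it was not possible to randomize the districts as clusters".

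**The concern.** With one district per arm, arm and district are the same variable. Difference-in-difference then rests wholly on the assumption that, without the intervention, contraceptive use would have changed equally in all four districts. A contraceptive stock-out, a change in staffing or another programme in one district breaks that assumption, and the analysis would report the result as an intervention effect. Districts that are socially, culturally and economically alike may have similar levels; that does not show they have equal trends, and a single baseline survey cannot check trends.

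All three contrasts share one control district, so a local event in West Gonja would move all three together. The same changes feed the cost-effectiveness comparison of the three intervention arms. The Discussion also says that interventions shown to be effective could be deployed in similar settings in Ghana and Africa. The wording of the causal claim therefore affects what readers do with the results.

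**Working it through.** **1. Degrees of freedom.** 4 districts − 4 arm effects = 0. The between-district variance of change cannot be estimated from these data, whatever the number of women.

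**2. What the planned figures cover.** With 170 women per arm and the district as cluster, Deff = 1 + (m − 1) × ICC gives ICC = 0.1/169 = 0.0006. If the design effect was meant for a unit inside the district, such as a community or facility, it does not address district-level variation at all. The article does not say which was intended.

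The figure of 170 was also checked. At 80% power (assumed, as none is stated), the two-proportion core of the article's formula gives 167.3 per arm, and 167.3 × 1.1/0.9 ≈ 204 after inflation. That discrepancy is a separate matter; nothing below depends on resolving it.

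**3. Illustrative false-positive rate.**

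Inputs from the article:
- p = 0.131, given as "which is the anticipated population proportion of modern contraceptive use at baseline";
- 170 women per arm less 10% loss = 153.

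Assumed, not in the article:
- within-woman correlation r = 0.3 to 0.5;
- SD of district-specific change τ = 1, 2, 3 or 5 percentage points.

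Under no effect, the variance from women alone is 4p(1 − p)(1 − r)/153, with p(1 − p) = 0.131 × 0.869 = 0.1138:
- r = 0.3: 4 × 0.1138 × 0.7/153 = 0.002083, SE 0.0456;
- r = 0.5: 4 × 0.1138 × 0.5/153 = 0.001488, SE 0.0386.

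Two districts enter each contrast, so the true variance adds 2τ². The false-positive rate is 2 × [1 − Φ(1.96 × SE_women/SE_true)].

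Example, r = 0.5 and τ = 0.03: SE_true = √(0.001488 + 0.0018) = 0.0573; 1.96 × 0.0386/0.0573 = 1.32; rate 18.7%.

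| SD of district change | Rate, r = 0.3 to 0.5 | Rate if the woman-level variance is inflated by 1.1 |
|---|---|---|
| 1 point | 6.1–6.6% | 5.0–5.4% |
| 2 points | 9.6–11.4% | 8.1–9.7% |
| 3 points | 15.1–18.7% | 13.2–16.7% |
| 5 points | 28.8–34.8% | 26.5–32.5% |

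**4. The same question for a positive result.** Suppose the hoped-for rise from 13.1% to 25.1% is observed exactly and the control district does not change, so D = 0.12. Significance is lost at τ* = √{[(D/1.96)² − SE²]/2}, where (0.12/1.96)² = 0.003748.

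The variance of a woman's change is 0.1138 + 0.1880 − 2r × 0.1463 in the intervention arm, where 0.1880 = 0.251 × 0.749 and 0.1463 = √(0.1138 × 0.1880). In the control arm it is 2 × 0.1138 × (1 − r).
- r = 0.3: SE² = (0.2141 + 0.1594)/153 = 0.002441; τ* = 2.6 points.
- r = 0.5: SE² = (0.1555 + 0.1138)/153 = 0.001761; τ* = 3.2 points.

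So even the full planned effect would not be significant if districts commonly diverge by about 3 points over a year for other reasons.

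**The case against.** The article is open about its structure. It says one district per arm, says twice that a cluster randomised trial gives stronger evidence, explains that the districts were purposively selected, and chose districts far enough apart to limit contamination. Standard errors and sensitivity analyses may be set out in a fuller plan. The SDs and correlations used above are not the article's. All of that stands, but it does not rescue the claim. The conceded limitation concerns the lack of randomisation, and allocating four districts to four arms at random would still leave zero degrees of freedom. A fuller plan could cluster on communities; it could not create replicate districts.

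Some stronger readings are tempting and are not supported:

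- **That the plan assumed an ICC of 0.0006.** This follows only if the district is the cluster, and no level is named.
- **That the plan specifies naive woman-level tests.** The unit of inference is not stated. What can be said is that any computable p-value must rest on within-district variation.
- **That a third of null comparisons would be declared significant.** This needs an SD of 5 points, for which the article gives no basis. At 1 point the inflation is slight.
- **That the inconsistent account of allocation creates the problem.** It is a separate reporting fault, which neither causes nor cures the confounding.

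**Conclusion.** The concern holds. The true-effect claim, and the assurance that similar districts make results comparable, assert a property that this design does not have. The general caveat about quasi-experiments does not disclose it.

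The identification failure follows from the stated design and needs no numerical assumption. Its numerical consequence does: it ranges from negligible to severe as the unknown SD of district-specific change goes from 1 to 5 points. Applying the 1.1 design effect to the variance lowers the false-positive rates only slightly. Nothing here shows that the districts did or will diverge; the point is that these data could not reveal it.

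**What to change.** 1. **Data processing and analysis.** Replace the true-effect sentence with one saying that the analysis estimates the difference in change between districts, and that this is attributable to the intervention only if no other district-specific change occurred.
2. **Context and Discussion.** Replace the assurance of comparability with an explicit parallel-trends assumption, and say that two surveys cannot test it.
3. **Limitations.** State that arm and district are fully confounded, and that intervals and p-values exclude district-level variation.
4. **Sensitivity analysis.** For each result, report the SD of district-specific change at which significance is lost, using the formula in step 4 of the working. Where routine district service counts are available, show pre-intervention trends as supportive evidence only; the article does not say that such counts identify women with disabilities.
5. **Separately, in Design.** Reconcile the two statements on allocation and describe one mechanism. Purposive selection of four districts does not by itself prevent allocating them to arms at random.

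The cost is some rewording, one short calculation per result and, if pursued, a request for routine data. Arms, sample and questionnaire are unchanged. The price is a weaker causal claim and wider stated uncertainty.
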